#### Time Scale

The cohort study will run for up to 4 years. The Programme is a five-year study, the first 6 months will be spent obtaining the necessary ethics and research governance approvals and the final year will be spent analysing the data, writing up and dissemination. The cohort study will therefore, in effect, run for three and a half years allowing at least 6 follow-up data points after the initial baseline assessments supposing that patients are enrolled into the cohort by 12 months from the start of the study.

#### Ethical approval

This study was granted ethical approval by the Bexley and Greenwich Research Ethics Committee (REC Reference: 07/H0809/38)

## Study 2: A Qualitative Study of patients' perceptions of distress and depression in patients with CHD

### Aims

The second study in the Up-Beat Programme is a qualitative study of the perceptions of depression and distress in patients with CHD who have significant depressive symptoms. The aim of this study is to elicit patients' perceptions of their psychological state as linked to their CHD and explore their views on appropriate treatments for distress or depression in the context of their CHD. A second aim is to explore particular distinctions they may make between distress and depression.

### Sample

Up to fifty people will be purposively sampled from the cohort study based on age, gender, practice, CHD status, and depression severity.

### Method/design

Consenting participants will have a semi-structured interview partly informed by an initial focus group of patients with symptoms of depression and co-morbid CHD. The interview will also cover:

• A description of the participant's current psychological state

• What treatments they think are appropriate for depression/psychological distress?

• How participants may prevent or take protective measures in the context of both CHD and distress/depression

• The views of participants on medication for both their heart condition and depression

### Analysis

The interviews will be audio-taped and transcribed verbatim. The analysis will be assisted by computer software, namely, NVivo7 (QSR International, 2006). A thematic analysis of the data will be conducted. The themes will be guided by the data but there will be two *a priori *areas of investigation; firstly the links made by the participant between their physical condition and their psychological state; secondly which treatments, if any, they think are appropriate? Discourse Analysis will be used to explore how participants think about their psychological state and to examine the language they use. Their use of language will be used to help develop a scale to differentiate between distress and depression as below.

### Developing a scale to differentiate distress and depression

A pilot scale, based on the analysis above, will be constructed that can be used to differentiate between distress and depression in primary care clinical practice. Focus groups will be convened to assess the validity of the scale. The scale will be factor analysed to see if there is a two-factor solution - one for distress and one for depression. The correlation of the scale, and sub-scales with a quantitative measures of depression will be assessed. A merged factor analysis on both the quantitative and patient-generated scales together will then be undertaken.

#### Ethical approval

This study was granted ethical approval by the Bexley and Greenwich Research Ethics Committee (REC Reference: 07/H0809/38)

## Study 3: A Qualitative Study of health professionals' perceptions of distress and depression in patients with CHD

### Objectives

The objectives of the third study in the Up-Beat programme are:

1. To explore primary care professionals' views on distress and depression in patients with CHD

2. To explore their current management strategies and attitudes to a range of treatments in relation to this patient group

3. To provide guidance on the design and implementation of a practice-nurse led case-management depression intervention.

### Method/design

Individual in-depth interviews will be conducted with up to 20 general practitioners and practice nurses in primary care centres in South London. The sample will be selected purposively to include professionals working in different settings (single-handed and group practices) serving areas of contrasting socio-economic, gender and ethnic characteristics. Potential participants will be invited to take part in an interview with the aim of exploring primary care professionals' perceptions of distress and depression in patients with coronary heart disease. An initial interview guide will be developed from the research literature. Key topics to be explored in the interviews are likely to include:

• Observations on the impact of distress and depression on help-seeking in patients with CHD

• Perceptions of the presentation of distress/depression in people with CHD, including patients' beliefs and attributions

• Age, gender, ethnic and cultural differences in the above

• Vulnerability and risk factors for depression in patients with CHD, including social and economic factors

• Current management strategies, including primary and secondary care interventions, patient self-care and non-medical or "life-style" strategies

• Attitudes to various treatment options, including practice-nurse led case-management

Interviews will be recorded on audiotape and transcribed verbatim. The interviewing and analysis procedure will be based on grounded theory principles in which theories are generated from themes identified in the analysis of participant interviews [32]. At least two researchers will read the transcripts of early interviews several times to immerse themselves in the data and then independently identify and give a descriptive "code" to relevant sections of the text. They will then compare their coding and any discrepancies will be discussed and resolved. An iterative procedure is followed in which new themes emerging from interviews are added to the coding frame and earlier transcripts recoded. New themes will be added to the interview guide to be explored in later interviews. The computer programme NVivo 7 (QSR International, 2006) will be used to process the transcripts, code themes systematically and explore the associations between them.

### Using key findings to inform the development of an intervention

Key findings from the interview study will be used in informing the choice and content of the pilot intervention for the randomised controlled trial using the following approach:

Choice of intervention

• Findings and recommendations from qualitative studies 2 and 3 will be assessed by an intervention working group, consisting of members of the research team and steering group. These will then inform the content and delivery of the case management intervention.

#### Patient participation via two focus groups

• A purposive sample of 8-10 qualitative interview participants will be selected to take part in 2 consecutive, focus groups, using the same sample for each group.

• The aim of the first group is to discuss the proposed pilot intervention and elicit suggestions for additions and/or alterations to the proposed content.

• The aim of the second group is to re-present the amended pilot intervention content and to elicit final comments and minor alterations that may be needed.

### Ethical approval

This study was granted ethical approval by the Bexley and Greenwich Research Ethics Committee (REC Reference: 07/H0809/38)

## Study 4: Feasibility study for a randomised controlled trial of case management for depression in primary care patients with symptomatic coronary heart disease

### Objectives

The objectives of this pilot are:

1. *Clinical efficacy of case management*

To explore whether case management for primary care patients with symptomatic coronary heart disease and depression, when delivered by mental health professionals may be more effective than treatment as usual.

2. *Sample size calculation*

Estimates of the location of the mean and variability around the mean (standard deviation) for the primary outcome measure (see measures) will be calculated. A conservative estimate using the 95% upper confidence limit will be used to inform the sample size calculation of the definitive RCT.

3. *To enable selection of the most appropriate primary and secondary outcome measures*. The pilot will also allow potential secondary outcome measures to be assessed.

4. *Integrity of the study protocol*

The pilot will allow all procedures for a definitive effectiveness RCT to be piloted. This will include testing:

• inclusion/exclusion criteria

• training of staff in the administration and assessment of the intervention.

5. *Testing data collection forms and questionnaires*

This will ensure that the questionnaires are acceptable to the participants, are comprehensible, appropriate, clearly defined and presented in a consistent manner. Patient information documents and consent forms will also be tested. Inter-rater reliability between researchers will be tested.

6. *Randomization procedure*

The randomisation process and acceptability of randomisation to primary care professionals and participants will be tested.

7. *Recruitment and consent*

The recruitment method will be tested and the consent rate for participants into the study calculated. Barriers to recruitment of both practices and participants will be explored. Follow-up rates will be calculated.

8. *To determine the acceptability of the intervention and the trial to practices and participants*. To determine the possible sources of contamination, and to develop a standardised manual for case management for use in the definitive RCT. To make an informal assessment of the degree to which the intervention can be standardised and whether therapist effects are likely to be a major factor.

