#### Methods/design

This is a naturalistic cohort study in primary care in South London, United Kingdom. Eligible consenting patients will be assessed at baseline and then at 6 monthly intervals for up to 4-years.

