#### Sample size calculation

The national prevalence of CHD in primary care as estimated by the Quality and Outcomes Framework (QOF) disease registers is 3.5%. We estimate that in patients with CHD, 20% will have a diagnosis of depression.

In a practice population of 10,000 people, we would therefore expect 350 patients with CHD of which 70 would be currently be depressed. Three practices with an average population of 10,000 patients will be recruited initially. Allowing for 80% participation, this will provide ~ 670 patients with CHD but no depression and ~168 patients with CHD and co-morbid depression. A cohort of this size would be large enough to estimate rates to acceptable limits on the basis of the above figures. The total sample size (~800) would produce up to 4800 data points over 4 years of follow-up at 6-monthly intervals (6 measures per person). This total sample size will be effectively somewhat smaller, firstly because of attrition and secondly because of the lack of independence of the repeated measures. Assuming an intra-person correlation of 0.2, the sample size would reduce by approximately 1/3 and if 20% dropout is also assumed, a total sample size of ~3130 data points would be collected, large enough to allow modelling of the associations between physical and mental illness as specified in the hypotheses.

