#### Setting and Practice recruitment

The study will be carried out in primary care. Practices in South London which are not participating in the cohort study will be recruited via the Greater London Primary Care Research Network (PCRN-GL) and invited to participate in the pilot study. We estimate from the results of the cohort study that we will need 10-15 practices each with around 10,000 patients in order to randomise between 30 and 50 participants per arm.

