#### Sample size

If we want to show a mean difference between intervention and control of ≥ 3 on the HADS Depression subscale, assuming a standard deviation around mean scores of 4, we will need 30 participants per group for 90% power at the 95% significance level. Therefore 60 participants (30 per arm) will be recruited into the RCT.

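### The plan names only the small pilot as the source of the HADS-D SD for the definitive trial and gives no source for the pilot's SD of 4, although the cohort measures the same scale; the pilot's stated 90% power is about 82% two-sided

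*Protocol article*

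**What the plan says.** **Definitive trial.** Study 4, Objectives, item 2 (Sample size calculation) has the pilot estimate the mean and SD of the primary outcome, and adds: "A conservative estimate using the 95% upper confidence limit will be used to inform the sample size calculation of the definitive RCT". No other source for the SD is named.

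**Pilot.** Study 4, Sample size, aims at a "mean difference between intervention and control of ≥ 3 on the HADS Depression subscale", "assuming a standard deviation around mean scores of 4", and concludes that "we will need 30 participants per group for 90% power at the 95% significance level". It goes on: "Therefore 60 participants (30 per arm) will be recruited into the RCT". The article gives no source for the SD and does not say whether the test is one- or two-sided.

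**Cohort.** Study 1, Methods/design, has patients "assessed at baseline and then at 6 monthly intervals for up to 4-years". Table 1 marks both the HADS and the Modified Rose Angina Questionnaire at baseline and at follow-up. Study 1, Sample size calculation, projects about "168 patients with CHD and co-morbid depression".

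**Link between the two.** The Background says that the first three studies will inform the pilot. Study 4, Setting and Practice recruitment, already draws on cohort findings: "We estimate from the results of the cohort study that we will need 10-15 practices". No passage applies cohort HADS data to either SD.

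**The concern.** An upper confidence limit on an SD from 60 patients or fewer carries a large allowance for small-sample error, and the definitive trial pays for that allowance in patients. The cohort holds the same scale in CHD-register patients under ordinary care in South London, at six-monthly intervals that coincide with the pilot's 6- and 12-month visits. Because it also records Rose angina, members resembling the trial population can largely be picked out. A second estimate would narrow the limit or, if it disagreed with the pilot, give a warning. The cohort could also supply the baseline-to-follow-up correlation, which is relevant to the regression modelling planned for the trial.

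For the pilot, an SD without a source leaves the stated power unsupported, and that power can be checked directly.

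**Working it through.** **1. The pilot's own figure.** Inputs from Study 4, Sample size: difference 3, SD 4, 5% level, 90% power. Per arm, n = 2(z_α + z_β)² × SD²/difference².

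- Two-sided: 2 × (1.960 + 1.282)² × 16/9 = 37.4, so 38 per arm.
- One-sided: 2 × (1.645 + 1.282)² × 16/9 = 30.4, so 31 per arm.

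The stated 30 is therefore approximately the one-sided answer. Power at 30 per arm, with standardised difference 3/(4 × √(2/30)) = 2.905:

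| Test at 5% | Normal approximation | t-test |
|---|---|---|
| Two-sided | 82.8% | 81.5% |
| One-sided | 89.6% | 89.0% |

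The two-sided t-test power for other SDs is 90% at 3.5, 72% at 4.5 and 63% at 5. These only show sensitivity; nothing in the article favours one of them over 4.

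**2. Size of the cohort source.** Three practices × 350 CHD patients × 0.8 participation = 840, and 20% of these gives 168 depressed. They come from the whole CHD register, whereas the trial also requires symptomatic CHD and a HADS-D cut-off. The number eligible is not given, so I take two ranges.

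- *Low.* The article expects 10–15 practices to yield 30–50 per arm. That is 60/15 = 4 to 100/10 = 10 randomised per practice, or 12–30 from three practices. This counts patients after trial consent, so the number eligible could be higher.
- *High (assumption).* 40–100% of the 168, which is 67–168.

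**3. Upper limit of the SD.** The limit is SD × √(df/χ²), where χ² is the lower 5% point on df degrees of freedom (one-sided 95%). Sample size is proportional to SD², so it is multiplied by df/χ². I assume 20% loss in both sources (the cohort's own dropout figure). That leaves 48 pilot patients in two arms (df 46), and m followed cohort members add m − 1. Each person is counted once, because repeat visits do not multiply the information on the between-person SD.

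| Source | df | SD × | N × | Saving against 48 pilot patients |
|---|---|---|---|---|
| Pilot, 60 analysed | 58 | 1.182 | 1.398 | – |
| Pilot, 48 analysed | 46 | 1.210 | 1.463 | reference |
| Pilot 48 + 10 (12 eligible) | 55 | 1.188 | 1.412 | about 4% |
| Pilot 48 + 24 (30 eligible) | 69 | 1.165 | 1.356 | 7% |
| Pilot 48 + 54 (67 eligible) | 99 | 1.134 | 1.285 | 12% |
| Pilot 48 + 134 (168 eligible) | 179 | 1.096 | 1.201 | 18% |

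The saving is 1 minus the ratio of the N factors, for example 1 − 1.201/1.463 = 0.18. The article does not say whether the 95% limit is one- or two-sided. Two-sided limits inflate more: N × 1.49 with 60 analysed and × 1.58 with 48.

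**4. Can the cohort stand alone?** With 50 eligible members (df 49) the one-sided factor on N is 1.44, wider than the 1.40 from 60 pilot patients. Below about 60 members, the cohort adds to the pilot but cannot replace it.

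**The case against.** The strongest reply is that nothing here contradicts anything. The pilot limit is to inform the definitive calculation, and no other source is excluded. A reader might infer that the definitive trial will rest on the pilot SD alone, but the text does not say so, and that trial will have its own protocol. The article is also condensed, so the absence of a source for SD 4 does not prove that cohort data were ignored. This stands, and it limits the point to what is named and what is not.

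A reader might also take the projected 168 as a ready sample for the trial's SD. It is not. It is a pre-recruitment projection for the whole register. The trial adds symptomatic CHD, a PHQ-2 screen that Table 1 does not list, a HADS-D cut-off and several exclusions. This stands too, and it is why the saving is given as a range.

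The upper limit is a deliberate safeguard and inflates N whatever the source (× 1.21 one-sided even with all 168 cohort patients), so only the excess is avoidable. The pilot has advantages the cohort lacks: trial consent, trial procedures and an intervention arm. Pooling assumes comparability, and a comparison of SDs at these sizes has little power to expose a difference. That argues against automatic pooling, though not against reporting the cohort value.

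Finally, it is tempting to say that the SD drives the pilot's power more than any other input. It does not: power depends on difference/SD, so the same proportional error in the 3 points matters as much. Nor would cohort data cure the shortfall at SD 4, which comes from sidedness.

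**Conclusion.** The point holds in a limited form.

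- Objective 2 names only the pilot as the source of the SD, and SD 4 is given without a source. A relevant second source exists in the programme and was already in use for planning practice numbers. This is a missed efficiency and a missing check, not a contradiction.
- The possible reduction in the definitive trial is about 4–7% with 12–30 eligible cohort members, and 12–18% with 67–168. Both ranges assume 80% followed, 48 pilot patients analysed, a one-sided 95% limit and comparable SDs. The eligible number is unknown. The pilot might also be larger, since Setting and Practice recruitment allows up to 50 per arm, which would shrink the gain.
- The firmest part is the power. With the stated inputs, 30 per arm gives about 82% for a two-sided 5% test, and about 89–90% only for a one-sided 5% test.

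**What to change.** 1. Reconcile the HADS-D entry cut-off first. Participant recruitment requires a score above 9, while Inclusion Criteria (Participants) requires 8 or more. The cohort subset cannot be defined until these agree.
2. In objective 2, add that the follow-up HADS-D SD and the baseline-to-6- and 12-month correlations will be estimated in cohort members who meet trial entry as far as the cohort's measures allow. Report them beside the pilot's within-arm SD and use them as supporting evidence for the definitive trial's SD. Pool only if the two groups are judged comparable, and keep the upper 95% limit.
3. In Study 4, Sample size, give the source of SD 4 or check it against the cohort value. State the sidedness and restate the power: about 82% two-sided with the present inputs.

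The cost is a few hours of analysis on data the programme collects anyway, and a few sentences of wording. The downside is that cohort members did not consent to a trial and none received the intervention, so comparability has to be judged before any pooling.

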### Method/design

This will be a pilot randomised controlled trial conducted in primary care. A descriptive account of the process and participants will be recorded.

#### Setting and Practice recruitment

The study will be carried out in primary care. Practices in South London which are not participating in the cohort study will be recruited via the Greater London Primary Care Research Network (PCRN-GL) and invited to participate in the pilot study. We estimate from the results of the cohort study that we will need 10-15 practices each with around 10,000 patients in order to randomise between 30 and 50 participants per arm.

#### Participant recruitment

All patients on practice case registers for CHD will be asked by their GP for consent to contact from a researcher. Those consenting will be contacted by a researcher and assessed for depression using the Patient Health Questionnaire-2[33] and for symptoms relating to CHD using the Modified Rose Angina Questionnaire [34]. Patients scoring 3 or more on the PHQ-2, and with symptomatic CHD will then be assessed further using the Hospital Anxiety and Depression Scale (HADS)[22]. If they score >9 on the depression scale of HADS they will be eligible to participate in the study. Those consenting to participate will then be randomised to either to the intervention (case management) or the treatment as usual (TAU) arm of the study.

#### Sample size

If we want to show a mean difference between intervention and control of ≥ 3 on the HADS Depression subscale, assuming a standard deviation around mean scores of 4, we will need 30 participants per group for 90% power at the 95% significance level. Therefore 60 participants (30 per arm) will be recruited into the RCT.

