#### Statistical analysis

Descriptive analyses will be used to provide summary estimates of outcome measures, focussing on the dropout rate at each time point, the order of magnitude of the effect of the intervention and the variability of the outcome measure at baseline. T-tests and regression modelling will be used to test whether there is a statistically significant difference between intervention and control groups. All analyses will be by intention to treat. While the sample size will not be sufficient to test clustering effects formally, sources of clustering will be identified so that they can be taken into account in a definitive RCT.

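### The pilot trial's 30 per arm gives about 82% power under a two-sided 5% test, not the stated 90%, and leaves no allowance for loss to follow-up

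*Protocol article*

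**What the plan says.** The Sample size section of Study 4 gives these inputs: "a mean difference between intervention and control of ≥ 3 on the HADS Depression subscale", "assuming a standard deviation around mean scores of 4", and the conclusion "we will need 30 participants per group for 90% power at the 95% significance level". The recruitment target follows directly: "Therefore 60 participants (30 per arm) will be recruited into the RCT". The section states no sidedness and makes no adjustment for attrition.

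Three other places bear on this:

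- The Statistical analysis section of Study 4 describes the test that the sample size serves: "T-tests and regression modelling will be used to test whether there is a statistically significant difference between intervention and control groups". It gives no direction.
- The Setting and Practice recruitment section of Study 4 estimates the number of practices needed "in order to randomise between 30 and 50 participants per arm".
- The Measures section of Study 4 sets follow-up at 1, 6 and 12 months. The objectives list follow-up rates among the things the pilot will calculate, and the analysis section will describe dropout at each time point.

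**The concern.** The stated power does not follow from the stated inputs under the test that most readers would assume. A standardised difference of 3/4 = 0.75 with 30 per arm falls clearly short of 90% power in a conventional two-sided comparison of means. The number of participants needed also becomes the number recruited without any step for loss, although outcomes are collected up to a year after randomisation.

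At stake is how a result is read. The pilot justifies its size by power, lists clinical efficacy as its first objective and plans significance tests. If the difference is not significant, the stated design implies a 10% chance of missing a true 3-point effect. Under a two-sided 5% test that chance is 17% to 18% with no loss at all, and higher with loss.

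**Working it through.** **Inputs.** From the Sample size section of Study 4: difference δ = 3, SD σ = 4, n = 30 per arm, power 90%. The significance level is taken as α = 0.05, which is how "90% power at the 95% significance level" must be meant. Equal allocation follows from 60 participants, 30 per arm. Sidedness is not given, so both versions are worked.

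**Formulas (normal approximation).**
- n per arm = 2(z_α + z_β)² / (δ/σ)², with (δ/σ)² = 0.75² = 0.5625
- power = Φ(0.75·√(n/2) − z_α)
- z_α is 1.960 two-sided or 1.645 one-sided; z_β is 1.2816 for 90% power.

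The t-test figures use the noncentral t distribution.

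**Step 1. Reproduce the plan's figure.**
- One-sided 5%: n = 2(1.645 + 1.2816)² / 0.5625 = 30.4, so 31 after rounding up (t-test: 31.1).
- Power at n = 30: 0.75·√15 = 2.905, and Φ(2.905 − 1.645) = 89.6% (t-test: 89.0%).

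The stated 30 per arm at 90% is therefore matched, to within rounding, by a one-sided 5% test.

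**Step 2. The same inputs, two-sided.**
- n = 2(1.960 + 1.2816)² / 0.5625 = 37.4, so 38 (t-test: 38.3, so 39).
- Power at n = 30: Φ(2.905 − 1.960) = 82.8% (t-test: 81.5%).
- The shortfall against 90% power is 8 to 9 analysable participants per arm.
- Difference detectable with 90% power at n = 30: 4 × 3.2416 × √(2/30) = 3.35 points (t-test: 0.851 × 4 = 3.40).

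**Step 3. Effect of loss.** The article gives no dropout rate for the pilot, so the rates below are assumptions that show a range.

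| Loss assumed | Analysable per arm | Two-sided power, t-test | One-sided power, t-test |
|---|---|---|---|
| 0% | 30 | 81.5% | 89.0% |
| 10% | 27 | 77.2% | 85.9% |
| 20% | 24 | 72.0% | 82.0% |

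**Step 4. Upper end of the planning range.** With 50 per arm and no loss, two-sided power is 96.0% by the t-test. With 20% loss, 40 per arm remain and power is 91.2%.

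**The case against.** **Sidedness is unstated, so the 90% may be a one-sided figure.** This is the strongest point against the concern. A one-sided 5% test reproduces the number closely, and the first objective has a direction, since it asks whether case management may do better than usual care. It stands to this extent: a reader might infer that the calculation is simply an arithmetic error, and the article does not support that, because a recognisable variant gives almost the same answer. It does not rescue the statement. No one-sided test is mentioned, the analysis section looks for a difference without direction, and a one-sided 5% test carries the same threshold as a two-sided 10% test, which a reader would not assume unprompted.

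**Regression on baseline could recover the power.** With a baseline correlation of about 0.45, the two-sided requirement falls to about 37.4 × (1 − 0.45²) = 29.8, or 30 per arm. But the article states no correlation, its calculation uses the spread of the scores themselves, and t-tests are named alongside regression.

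**Attrition is for the pilot to measure.** This is fair, and it limits what can be claimed. A reader might take 72% as the real power because the sample size calculation for the Study 1 cohort uses a 20% rate ("if 20% dropout is also assumed"). That rate belongs to repeated measurements in an observational cohort followed for up to four years, and nothing applies it to the 12-month pilot. What stands is that recruited equals needed.

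**The 30 to 50 range.** A reader might also infer that the two Study 4 sections contradict each other. They do not clearly do so: 30 is the lower end of a range used to plan the number of practices. The relation between the two figures is left unsaid, but it is not an inconsistency.

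**It is a pilot.** Most objectives concern procedures, recruitment, acceptability and estimating variability, and the analysis leads with description. That lowers the severity. It does not make the power statement correct.

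**Conclusion.** The point holds in conditional form. Given a 3-point difference, SD 4, equal allocation and a two-sided 5% test, 30 analysable per arm gives about 82% power (81.5% to 82.8%), and 90% needs 38 to 39 per arm. The two-sided test is an inference from the non-directional wording of the analysis section and from convention; the article does not state it. If a one-sided 5% test was meant, power is 89.0% to 89.6% and the gap is only rounding, but the test would then have to be declared.

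The absence of any allowance for loss is plain in the text. Its size is not known: about 77% at 10% loss and about 72% at 20% loss are illustrations under the two-sided test, not properties of this design. The severity is moderate, because power is a secondary consideration in a study meant chiefly to test feasibility and inform a definitive trial.

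**What to change.** In the Sample size section of Study 4:

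1. State the sidedness and give the level as 5%.
2. For a two-sided test, restate the power as about 82% for a 3-point difference with SD 4 and 30 analysable per arm. It can be added that 90% power applies to a difference of about 3.4 points.
3. Say that 30 per arm is before attrition and that power falls with any loss. If a figure is shown, label the loss rate as an assumption.
4. Say whether 30 per arm is the minimum of the 30 to 50 range in the Setting and Practice recruitment section.

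If a one-sided 5% test was in fact intended, declare and justify it here and in the Statistical analysis section.

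The cost is wording only. The stated power becomes less favourable, but no extra participants and no change to design or analysis are needed. If the sponsor prefers to keep 90% two-sided, 38 to 39 analysable per arm already lies within the 30 to 50 range, though the 60-participant target would have to rise.
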